### Sample size

2.4

The number of participants was calculated on the basis of comparative studies that verified the effects of massage on growth because previous studies on massage intervention using a massage chair for growth promotion are rare. Thirty children per group were selected for judging the growth effect of massage in previous studies.^[12,13]^ We calculated the appropriate total number of participants to be 38 by considering the 20% dropout rate.

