#### Bone age

2.8.2

On hand radiography at visits 2 and 5, bone age will be computed using the Tanner-Whitehouse (TW) method. The maturity of the hand ossification centers will be assessed as a radius-ulnar-short bone (RUS) score from 0 to 1000 as compared with the bone age chart according to sex and age.^[15]^ Two-year-old boys have a RUS score of 42, and 2-year-old girls have a RUS score of 126. The RUS score of 1000 is computed for 16.5-year-old boys and 15.0-year-old girls. The TW3 RUS score was based on the American, Argentine, Belgian, British, Italian, Japanese, and Spanish surveys between 1960 and 1995. The TW3 RUS score will be calculated by researchers who have been trained for > 3 months before assessment.

Predicted adult height will be calculated from the measured height and RUS score using the TW3 equations, which were developed according to boys, girls before menarche, and girls after menarche. The height SDS for bone age will be determined according to the 2017 Korean growth chart.

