### Statistical analyses

2.9

Outcomes will be analyzed with a full analysis set (FAS) and per protocol set (PPS). The FAS targets all participants whose heights can be measured after starting the intervention and have no major violation of inclusion criteria. PPS targets all the participants who have been treated with the massage chair for >118 days (70% of the total 168 days). The safety analysis targets all participants with available safety data obtained by phone or visit.

Continuous data will be arranged as representative values such as mean and standard deviation. Height percentile, height SDS, predicted adult height, seated height-to-standing height ratio, and BMI will be tested by using the paired *t* test or Wilcoxon signed-rank test. The final height and weight will be measured by using a 1-sample *t* test or Wilcoxon signed rank-test from the parameters after 24 weeks of initial percentile. The final bone age will be tested by using a 1-sample *t* test or Wilcoxon signed rank-test, from the age after 0.5 years of the initial bone age. AEs will be described as frequency, percentage, and 95% confidence interval for the occurrence rate in all the participants. The difference in the incidence of AEs between before and after intervention will be tested by using a *χ*^2^ test or Fisher exact test. A secondary analysis will be conducted by grouping according to boys, girls before menarche, and girls after menarche. If necessary, analysis of covariance will be used.

The significance level is 0.05 for all the statistical tests, and 2-tailed tests will be performed. Missing values will be imputed using the last-observation-carried-forward method.

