## Discussion

3

Massage had some effects on growth in randomized controlled trials (RCTs) or quasi-RCTs.^[16]^ It was used alone or with swimming, oral administration, plaster therapy, or auricular acupuncture. The most frequently used massage method was spine pinching, which promotes gastric fluid secretion, gastrointestinal peristalsis, and digestive ability for carbohydrates and proteins. However, previously studied growth-promoting massages have individual differences in effect depending on the skill of the practitioner, due to the nature of manual therapy. This is the first study to verify the effect of standardized massage using massage chair on growth by stimulating the spine and knees with fixed strength and frequency.

BEG-100 targets children whose heights range from 130 to 170 cm, but it is most appropriately manufactured for a 150-cm height. We determined to enroll 11-year-old Korean children because the average heights of 11-year-old Korean boys range from 144.7 to 150.8 cm and those of 11-year-old Korean girls range from 145.8 to 151.3 cm. The intervention period was set to be 24 weeks, which is the most frequent intervention period in previous studies that reported the effect of massage on growth. Standing and seated heights will be measured to see changes in height, height percentile, height SDS, growth rate, and seated height-to-standing height ratio. Hand radiography will be performed to identify changes in bone age, predicted adult height, and height SDS for bone age. Through weight measurements, we will confirm changes in weight, weight percentile, and BMI. The safety of BEG-100 will be investigated through a comparison of voluntarily reported AEs before and after the intervention.

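### Carrying the last value forward while testing final height, weight and bone age against a reference fixed at 24 weeks or 0.5 year builds in an average shortfall for each analysed child with a missing final value

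*Protocol article*

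**What the plan says.** All of this is in the protocol article.

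- **Missing data (Statistical analyses):** "Missing values will be imputed using the last-observation-carried-forward method". No outcome is exempted.
- **Reference for final height and weight (same section):** a one-sample test "from the parameters after 24 weeks of initial percentile", which I read as the value expected 24 weeks later on the child's starting percentile.
- **Reference for final bone age (same section):** "from the age after 0.5 years of the initial bone age". Neither reference is tied to the date of the last measurement.
- **Bone-age films (Bone age):** "On hand radiography at visits 2 and 5, bone age will be computed using the Tanner-Whitehouse (TW) method".
- **Analysis sets (Statistical analyses):** "The FAS targets all participants whose heights can be measured after starting the intervention and have no major violation of inclusion criteria". The PPS takes children "treated with the massage chair for >118 days (70% of the total 168 days". Neither definition asks for a week-24 measurement.
- **Expected attrition (Sample size):** "We calculated the appropriate total number of participants to be 38 by considering the 20% dropout rate".
- **Growth at this age (Discussion):** "the average heights of 11-year-old Korean boys range from 144.7 to 150.8 cm"; the girls' range is 145.8 to 151.3 cm.

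**The concern.** LOCF treats a child as if growth stopped at the last visit attended. In 11-year-olds, whose average height rises by several centimetres a year, that is wrong in a known direction. Here the frozen value is set against a target that includes the full 24 weeks of expected growth, so the difference contains the growth that was never observed.

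For height and weight this pulls the mean down. It can hide a real gain or produce a significant apparent deficit. For bone age it mimics slower maturation. LOCF therefore cannot be defended as simply cautious: the height error runs against the device, while the bone-age error is one that some readers might take in its favour.

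**Working it through.** **The plan's own figure.** 30 / (1 - 0.20) = 37.5, rounded up to 38, as stated. The planning allowance is thus up to 8 of 38 children without final values.

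**Growth rate.** If each range in the Discussion spans one year:
- boys: 150.8 - 144.7 = 6.1 cm/year; girls: 151.3 - 145.8 = 5.5 cm/year; midpoint 5.8.
- 24 weeks = 168 / 365.25 = 0.46 year, so expected growth is 5.5 x 0.46 = 2.53 cm to 6.1 x 0.46 = 2.81 cm.

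**Growth missed per carried height.** The weeks of the intermediate visits are not in the text; I assume 8, 16 and 24.
- last seen at week 16: rate x 56 / 365.25 = 0.84 to 0.94 cm (0.89 at 5.8 cm/year)
- last seen at week 8: rate x 112 / 365.25 = 1.69 to 1.87 cm (1.78 at 5.8 cm/year)

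**Bias in mean height** = (number carried / 38) x mean missed growth. With equal numbers last seen at weeks 8 and 16, mean missed growth is (0.89 + 1.78) / 2 = 1.33 cm.

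**Chance of a false significant deficit.** Simulation of the two-sided 5% one-sample t test with no true effect; the SD of a child's deviation from the reference is assumed to be 0.8 to 1.0 cm.

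| Carried forward | Height bias | False significant deficit (nominal 2.5%) |
|---|---|---|
| 2 of 38, week 8 or 16 | 2/38 x 1.33 = -0.07 cm | about 5-6% |
| 4 of 38, week 8 or 16 | 4/38 x 1.33 = -0.14 cm | about 11-13% |
| 8 of 38, from all at week 16 to a mix of weeks 8 and 16 | 8/38 x 0.89 = -0.19 cm to 8/38 x 1.33 = -0.28 cm | about 18-41% |

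The percentages move by a few points with the spread assumed for carried values. If they vary as much as observed final values, the last two rows become about 10-12% and 17-38%. If all 8 were last seen at week 8, the bias would be 8/38 x 1.78 = -0.37 cm.

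**Power for an assumed true gain of 0.5 cm.**
- 30 completers without LOCF: about 76% (SD 1.0) to 91% (SD 0.8).
- 8 of 38 carried: about 9% (mixed weeks) to 47% (all at week 16).
- In the mixed case the estimate is about +0.17 cm: 0.50 - 0.28 (missed growth) - 0.05 (8/38 x half of 0.5 cm, the effect not accrued after stopping).

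**Bone age.** With films only at visits 2 and 5, a missing final film leaves just the baseline value to carry. The child contributes baseline - (baseline + 0.5) = -0.5 year. With 8 of 38 carried the bias is -0.5 x 8/38 = -0.105 year; with 4 of 38 it is -0.053 year. This needs no assumption about visit weeks.

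**PPS.** A child who stops at day 119 meets the use threshold with 168 - 119 = 49 days to go. Even if measured that day, the height is short by 5.5 x 49 / 365.25 = 0.74 cm to 6.1 x 49 / 365.25 = 0.82 cm.

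**Weight.** The mechanism is the same, but the document gives no weight gain per year, so it cannot be sized.

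**The case against.** The best counter-case accepts the mechanism and disputes scope and size. Most of it stands.

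- **Not every dropout counts.** A reader might infer that each one adds a deficit. The FAS requires a height taken after the intervention starts, so a child who leaves before that adds nothing. The shortfall is also an average: a child already above the 24-week expectation would show none.
- **Not every growth measure is affected.** Height percentile and SDS are tested by paired tests. If the score itself is carried, the imputed change is no further shift. The deficit arises only if raw height is carried and re-scored at the later age, and the text does not say which. Growth rate is height difference divided by days, so it can use actual time.
- **The power loss is easily exaggerated.** Comparing with 38 fully observed children (85-96%) charges ordinary attrition to LOCF. Thirty completers are the fair comparator.
- **Eight carried values is near the worst case.** The 20% is a planning allowance. With 2 carried, the height bias is small.
- **Bone age is not a growth deficit.** The artefact is apparent slower maturation. That it would be read as a benefit is inference; the document does not say so. The -0.5 year also assumes no extra film at withdrawal, and the schedule figure is not visible.
- **The study calls itself a pilot** and says the growth effect cannot be proved without a comparison group. That limits the claims, but a pilot for later randomised trials still needs an undistorted estimate.

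None of this removes the mismatch between a frozen value and a fixed later reference.

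**Conclusion.** The concern holds for final height, weight and bone age as tested against fixed references. Neither the FAS nor the PPS corrects it. The direction follows from the protocol's own wording. The bone-age size, -0.5 year per missing final film, follows from the film schedule.

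The height figures are scenarios. They rest on a growth rate read from the Discussion and on assumed visit weeks, residual SD, true effect, and number and timing of missing finals. A reader might infer that the trial will probably report false stunting or has almost no power. The documents do not support that: those results need close to the full dropout allowance, with some children leaving as early as week 8. With 2 of 38 carried, the false-deficit rate is about twice nominal and the bias under 0.1 cm. The flaw is definite, its size is conditional, and it can be avoided at almost no cost.

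**What to change.** Remove LOCF for height, weight and bone age.

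- **Height and weight:** analyse SDS from all visits at exact age with a linear mixed model and estimate the week-24 change from it. This is valid if data are missing at random. A simpler alternative is to compare each child's last measurement with the reference at that measurement's actual date; this describes deviation at last contact rather than at week 24.
- **Bone age and predicted adult height:** use children with both films, and compare bone-age change with actual elapsed time. This also removes a separate small mismatch: 24 weeks is 0.46 year, so the 0.5-year reference puts even completers about 0.04 year low.
- **If LOCF is kept as a sensitivity analysis:** carry the SDS forward, not centimetres, kilograms or bone-age years, and say so.

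Cost: analysis wording only, since height and weight are already measured from screening to close-out. The bone-age sample falls to children with both films, about 30 at the planned dropout, which the inflation from 30 to 38 already allows for.

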### Data monitoring

2.10

The data monitoring committee is composed of three Korean medicine doctors employed in Kyung Hee University Korean Medicine Hospital but who have no participation in this study. They will conduct monthly monitoring of document reporting, protocol violation, and AEs during the study. Any interim analyses and guidelines for discontinuation will follow the standard operating procedure of the Korean Medicine Clinical Trial Center of Kyung Hee University Korean Medicine Hospital. Issues found will be discussed with the principal investigator.

## Discussion

3

Massage had some effects on growth in randomized controlled trials (RCTs) or quasi-RCTs.^[16]^ It was used alone or with swimming, oral administration, plaster therapy, or auricular acupuncture. The most frequently used massage method was spine pinching, which promotes gastric fluid secretion, gastrointestinal peristalsis, and digestive ability for carbohydrates and proteins. However, previously studied growth-promoting massages have individual differences in effect depending on the skill of the practitioner, due to the nature of manual therapy. This is the first study to verify the effect of standardized massage using massage chair on growth by stimulating the spine and knees with fixed strength and frequency.

BEG-100 targets children whose heights range from 130 to 170 cm, but it is most appropriately manufactured for a 150-cm height. We determined to enroll 11-year-old Korean children because the average heights of 11-year-old Korean boys range from 144.7 to 150.8 cm and those of 11-year-old Korean girls range from 145.8 to 151.3 cm. The intervention period was set to be 24 weeks, which is the most frequent intervention period in previous studies that reported the effect of massage on growth. Standing and seated heights will be measured to see changes in height, height percentile, height SDS, growth rate, and seated height-to-standing height ratio. Hand radiography will be performed to identify changes in bone age, predicted adult height, and height SDS for bone age. Through weight measurements, we will confirm changes in weight, weight percentile, and BMI. The safety of BEG-100 will be investigated through a comparison of voluntarily reported AEs before and after the intervention.

The study protocol has a few limitations. First, a comparison group was not included. Although the data from the intervention group will be compared with national standard statistical data, the growth effect of the massage chair cannot be proved because of the absence of a local comparison group. This study is only a pilot study for future randomized controlled trials. Second, the frequency of the intervention is difficult to ascertain. Massage using BEG-100 will be performed in the participants’ homes, and the frequency of the intervention will be confirmed by the participants’ reports. The participants might report more or less frequency about the intervention, but this is unlikely because of the absence of a related reward or penalty. Third, although nutrition balance and exercise time will be checked in every visit after the BEG-100 intervention, other confounding factors regarding growth such as stress and sleep may influence the results.

Massage stimulates skin sensory receptors, subcutaneous tissues, blood, lymph, and tissue fluid; therefore, increasing local microcirculation and parasympathetic nervous system.^[17]^ It also increases food absorption and basal metabolism through enhanced vagal activity, gastric motility, and insulin and insulin-like growth factor-1 levels.^[18]^ Spine massage promotes local skin protein expression, thereby regulating the local immune function.^[19]^ Moderate pressing stroke, and flexion and extension of the extremities increased bone mineral density and bone growth.^[7]^ However, these growth effects of massage have been mainly demonstrated in premature babies. Our research will provide information on the potential effects and safety of massage using a massage chair for growth in teenagers.
